## Abstract

**Background:**

Stroke represents one of the most costly and long-term disabling conditions in adulthood worldwide and there is a need to determine the effectiveness of rehabilitation programs in the late phase after stroke. Limited scientific support exists for training incorporating rhythm and music as well as therapeutic riding and well-designed trials to determine the effectiveness of these treatment modalities are warranted.

**Methods/Design:**

A single blinded three-armed randomized controlled trial is described with the aim to evaluate whether it is possible to improve the overall health status and functioning of individuals in the late phase of stroke (1-5 years after stroke) through a rhythm and music-based therapy program or therapeutic riding. About 120 individuals will be consecutively and randomly allocated to one of three groups: (T1) rhythm and music-based therapy program; (T2) therapeutic riding; or (T3) control group receiving the T1 training program a year later. Evaluation is conducted prior to and after the 12-week long intervention as well as three and six months later. The evaluation comprises a comprehensive functional and cognitive assessment (both qualitative and quantitative), and questionnaires. Based on the International classification of functioning, disability, and health (ICF), the outcome measures are classified into six comprehensive domains, with participation as the primary outcome measure assessed by the Stroke Impact Scale (SIS, version 2.0.). The secondary outcome measures are grouped within the following domains: body function, activity, environmental factors and personal factors. Life satisfaction and health related quality of life constitute an additional domain.

**Current status:**

A total of 84 participants were randomised and have completed the intervention. Recruitment proceeds and follow-up is on-going, trial results are expected in early 2014.

**Discussion:**

This study will ascertain whether any of the two intervention programs can improve overall health status and functioning in the late phase of stroke. A positive outcome would increase the scientific basis for the use of such interventions in the late phase after stroke.

**Trial registration:**

Clinical Trials.gov Identifier: NCT01372059

## Background

Stroke is a multifaceted and complex condition. It is the second leading cause of death and a major cause of long-term disability worldwide
[1,2], constituting an enormous cost to the society. Stroke often results in physical
[3-6], cognitive
[3,6], psychological
[7-15], and social impairment
[13,16,17] and the personal burden of being a stroke survivor is often devastating and has major consequences for the patient’s quality of life
[18].

Previous research in the field has primarily focused on treatment in the acute phase and rehabilitation during the first year after stroke. Experimental animal research and neuroimaging studies have provided insight into various aspects of neural plasticity, i.e. possible mechanisms of structural and functional neural reorganisation in the brain following injury
[19-21]. The understanding of the brain’s plastic properties has lead to the emergence of new approaches in stroke rehabilitation
[22]. A number of animal studies demonstrated that various forms of multimodal (multisensory) stimulation or an enriched environment, facilitate multiple processes in the brain and are associated with improved functional outcome and neural plasticity
[23-33].

There is a growing interest in using music and rhythm as a stimulus for neurotherapy
[34,35]. Music therapy is the clinical and evidence-based use of music interventions to accomplish individualized goals within a therapeutic relationship by professionals who have completed an approved music therapy program
[36]. The new approach to clinical practice and research, known as Neurologic Music Therapy (NMT)
[37,38] is based on a neuroscience model of music perception and production, and the influence of music on functional changes in the brain and behaviour functions
[39]. Using standardized treatment protocols, NMT is a therapeutic application of music to cognitive, sensory, and motor dysfunctions due to neurologic disease of the nervous system
[40]. Music Supported Therapy and Melodic Intonation Therapy were proposed to induce plastic changes in the brain in terms of functional connectivity and neural reorganization in the sensorimotor cortex
[41-43], as well as in white matter tracts
[44].

Schneider et al.
[45,46] showed that Music Auditory Stimulation leads to improvements in speed, precision and smoothness of movements in fine as well as gross motor skills in stroke patients. Further, music therapy has a positive effect on mood in patients with stroke
[47-49]. Rhythmic Auditory Stimulation can enhance gait ability
[50-52], flexibility
[49], as well as functional motor performance of the paretic upper extremity
[53]. Despite the growing body of scientific evidence in favour of the use of music therapy in neurorehabilitation, there is a need for better understanding of the impact of the therapy programs incorporating music and rhythm.

Therapeutic riding (TR), also named Equine-Assisted Therapy and Adaptive Riding uses equine-assisted activities for the purpose of contributing positively to cognitive, physical, emotional and social well-being of people with disabilities
[54]. In Sweden, TR is used both in neurologically disabled adults and children. TR incorporates mounted activities and exercises, and the patient actively interacts and influences the horse. The movement of the horse affects the patient both physically and psychologically. In contrast to hippotherapy
[55], defined as a physical, occupational, and speech-language therapy treatment strategy that utilizes equine movement as part of an integrated intervention program to achieve functional outcomes, TR teaches specific skills and techniques associated with riding a horse. The primary focus is on developing balance, body awareness and muscle tone in the rider by responding and interacting passively to the horse’s multidimensional movement. Given the varying degree of impairment present among stroke survivors, TR has some risks, as do other animal-assisted therapies. However, in accredited centres these risks are minimal and the benefits are likely to outweigh them.

There is limited scientific evidence suggesting that TR is effective. Previous studies indicate that TR and hippotherapy are beneficial for improving postural control in children with cerebral palsy
[56-58], patients with multiple sclerosis
[59,60], and spinal cord injuries
[61]. A positive effect of hippotherapy associated with conventional physical therapy was shown on gait training in post-stroke hemiparetic individuals
[62]. The ultimate goals of rehabilitation interventions for stroke survivors as well as the measurement level selection can be guided by the International classification of functioning, disability, and health (ICF)
[63-65], namely health-related domains that are assessed from the body, individual and societal perspectives: the domain body functions and structure and the domains of activity and participation. Functioning is an umbrella term encompassing all of the domains mentioned above
[66], and participation is considered to be a critically important outcome indicator in the rehabilitation context
[67].

Based on the fundamental principles of brain plasticity, we developed rhythm and music-based therapy and TR protocols and designed a three-armed randomized controlled trial to evaluate whether improvement in overall health status and functioning can be achieved in the late post stroke phase by using these multimodal therapy programs. We selected measures most likely to capture change in the targeted aspects of interventions, linked them to the ICF model, and hypothesize that both methods have primary effects on the individuals’ level of participation. To identify potential biomarkers predictive of outcome, blood samples taken at several time points during the study will be analysed. Such biomarkers might ultimately aid to individually tailor neurorehabilitation programs.

### Study aims and objectives

The aim of this study is to investigate whether overall health status and functioning can be improved in community-dwelling individuals in the late phase of stroke through rhythm and music-based therapy or TR. The primary aim is to investigate whether improvement in terms of participation is attained after completion of these therapy programs. Secondary aims are to investigate whether these two interventions have a positive effect on body function, activities, environmental and personal factors, as well as life satisfaction and health related quality of life in the late phase of stroke. In addition, using interviews and focus groups as a qualitative research approach, this study aims at understanding which factors related to the therapies delivered can positively affect stroke survivors’ lives. We also aim at the identification of potential biomarkers in plasma predictive of outcome.

## Methods

### Study design

A single blinded three-armed randomized controlled trial is designed with the aim to evaluate whether it is possible to improve overall health status and functioning of individuals in the late phase of stroke (1-5 years after stroke) through a rhythm and music-based therapy program or TR (Trial registration: Clinical Trials.gov Identifier: NCT01372059). The term *single blinded* refers to the evaluators in the trial being unaware of the nature of the treatment the participants are receiving. About 120 individuals will be consecutively and randomly allocated to one of three groups: (T1) rhythm and music-based therapy program; (T2) TR; or (T3) control group that receives the T1 therapy a year later. Evaluation is conducted prior to and after the 12-week long intervention, and three and six months after completed intervention. The evaluation comprises comprehensive functional and cognitive assessment (both qualitative and quantitative), and questionnaires. Blood samples will be collected pre-, post intervention and at the three and six month follow-up with the aim of identifying potential biomarkers predictive of outcome. Based on the International classification of functioning, disability, and health (ICF), the outcome measures are classified into six comprehensive domains, with participation as the primary outcome measure assessed by the Stroke impact scale (SIS, version 2.0.). The secondary outcome measures are grouped within the following domains: body functions, activity, environmental factors and personal factors. Life satisfaction and health related quality of life constitute an additional domain. The trial design is illustrated in Figure
1. Ethical approval was granted by the Regional Ethical Review Board in Gothenburg (Ref number: 698-09) and the study is conducted in accordance with relevant ethical guidelines.

**Figure 1 F1:**
[figure not shown]
**Flowchart illustrating trial design.** *) Including selected participants.

### Recruitment and selection of participants

The participants are recruited from a comprehensive hospital-based register covering all patients who were treated for ischemic or hemorrhagic stroke at Sahlgrenska University Hospital, Gothenburg, Sweden. The search criterion is limited to individuals who suffered from stroke 1 to 5 years prior to their potential inclusion in the clinical trial. By searching through hospital files, an authorized research coordinator selects persons potentially eligible for the trial. These individuals are then contacted through a letter containing information about the research trial and its implementation. A few days later, each individual receives a follow-up telephone call from the research coordinator. The research coordinator informs the individuals about the study, including requirements, nature and potential benefits of the two therapy programs. Consenting interested subjects are screened by a telephone interview in order to ascertain eligibility for the trial. Further, we record parameters of general health (past and current), medication, physical and cognitive function, stroke-related disability, rehabilitation history, history of previous stroke or other diseases or injuries. Also, information about social relationship, work situation, living arrangements, and the need for transportation service for disabled is obtained.

Individuals who have met the study criteria are invited for a personal appointment with a specialist in rehabilitation medicine for a more detailed screening assessment and interview prior to inclusion. A prior history of stroke is accepted if the previous stroke event affected the same hemisphere as the most recent stroke. Inclusion in the trial requires acceptance of allocation and compliance to either of the three treatment arms, even though allocation to group 3 means that treatment would be delayed by a year. Participants are informed that they can withdraw from the study at any time. After the screening procedure, eligible individuals are included in the trial. Once included, all participants sign a written informed consent form. Selection criteria for trial eligibility are presented below:

Inclusion criteria

– Aged 50 − 75 years

– Disability grade 2 or 3 on MRS*)

– Being in the late-phase of stroke (1 − 5 years after an ischemic or hemorrhagic stroke with initial presence of hemispheric impact/symptoms)

– Subarachnoid hemmorhage with initial presence of hemispheric impact/symptoms

– Ability to understand written and oral information and instructions in Swedish

– Having an own housing

– Ability to travel to the place of intervention and evaluation

– No need for personal assistance in activities of daily living while participating in the treatment (going to the toilet, transport/transportation services for disabled, walking)

– Accepting allocation to either of the three groups which might mean accepting staying without any of the treatment procedures for one year

Exclusion criteria

– Disability rated ^<^ 2 or ^>^ 3 on MRS*)

– An ischemic or hemorrhagic stroke or subarachnoid hemmorhage without hemispheric impact/symptoms

– Pronounced fear of horses or allergy constituting a risk for the patients to participate in the therapeutic riding

– Heart conditions that constitutes a risk for the individual to participate in the interventions

– Non-controlled epileptic seizures constituting a risk for the patients to participate in the interventions

– Lack of cognitive and/or verbal ability or visual impairment that makes it difficult for the individual to understand instructions and/or evaluation

– Total paralysis of the affected arm

– Injury or disease that makes the individual not suitable for the trial

– Weight ^>^ 97 kg (to optimize safe horseback riding)

– Having more than a half-time employment

– Injury, disease or addiction that make the individual not suitable for the trial

– Participation in RGRM or therapeutic riding during the year prior to inclusion

– Having an additional stroke within the past year (TIA is however accepted)

– Lack of willingness to participate in any of the treatment methods

– Living ^>^ 80 km from Gothenburg

– Dependent on transportation services for disabled across the community border which is not allowed according to the regulations

*) Modified Rankin Scale: An ordinal disability rating scale ranging from zero to 6 (0 = no symptoms). MRS grade 1: No significant disability despite symptoms; able to carry out all usual duties and activities; MRS grade 2 = *Slight disability*: unable to carry out all previous activities but able to look after own affairs without assistance; MRS grade 3 = *Moderate disability*: requiring some help, but able to walk without assistance; MRS grade 4: *Moderately severe disability*: unable to walk without assistance and unable to attend to own bodily needs without assistance; MRS grade 5: *Severe disability*: bedridden, incontinent and requiring constant nursing care and attention; MRS grade 6: Dead.

### Randomization, allocation concealment and blinding

As gender and laterality might influence outcome in clinical studies
[68], the randomization is stratified with respect to gender and hemispheric location of the stroke (right or left hemisphere). Prior to inclusion of participants, a statistician performed randomization using random permuted blocks for each of the 2 × 2 strata. Until the completion of the last long-term follow-up, only the project leader and two persons responsible for the interviews and focus groups will have access to the information on group allocation. Due to the nature of the therapy programs, blinding of the participants and treating therapists is not possible. However, all the independent evaluators are blinded with respect to group allocation, and the participants are not informed of primary outcome measure or the study hypothesis. To maintain group allocation confidential, participants are requested prior to each assessment phase to not reveal allocation or therapy content to the evaluators. Participants scheduled for qualitative studies are told that they must not talk to the evaluators about participation in interviews and focus groups. Furthermore, the interviews and focus groups are performed in a way that does not reveal participants’ allocation.

### Sample size

The calculation of sample size is based on a clinically relevant difference to be detected across the two main arms of the trial with an alpha level of 5% and a power goal of 80%. A Chi-square test was used for statistical calculations in Nquery 6.0. The required sample size was determined on the basis of one of the items included in the primary stroke-specific, comprehensive, health status outcome measure - Stroke Impact Scale (SIS). SIS measures the aspects of stroke recovery which were found to be important to patients and caregivers as well as stroke experts. The questions of the SIS are broken down into eight domains: strength, hand function, mobility, activities of daily living, emotion, memory, communication, and social participation. The first four of these domains may be combined into one physical domain, but in order to more clearly track changes based on the patient’s particular set of symptoms, the other four items are scored separately. One additional item is included in the SIS to assess the subject’s overall perception of recovery. This item 9 – “Stroke recovery” is presented in the form of a visual analogue scale from 0 to 100 where 0 indicates “no recovery” and 100 indicates “full recovery”.

Based on a previous study indicating that the item of stroke recovery in SIS is a good measure of individual patient’s changes due to rehabilitation
[69], and the heterogenic characteristic of the study population, the required sample size was determined based on this specific item. The minimal important difference (MID) was determined a priori. On the basis of previous estimates
[70], MID was set at 10 points of the total range of the scale in item 9. Thus, a change of 10 points is considered to represent a meaningful difference. An absolute difference between the two groups of 30% is defined to be a clinically meaningful difference with regard to the item stroke recovery in SIS. Based on this estimate, at least 41 patients would be required in each of the three groups for the results to satisfy the power criteria of 80%.

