### Statistical analysis

Outcome variables will be analyzed according to an intention-to-treat model including all randomized patients for whom a baseline value exists in the primary outcome variable. Those who withdraw will be assigned an outcome score identical to their baseline score i.e. no change. In addition, the per-protocol analysis will be restricted to the participants who complete the treatment program and remain in the group to which they were randomly assigned, and have available data on the primary and secondary outcome variables. Patients will be excluded from the per-protocol analysis if they withdrew during the intervention phase or undergo a co-intervention during the three-month intervention phase. Reasons for early withdrawal will be noted.

Baseline and demographic characteristics will be summarized using descriptive statistics. Statistical difference between treatments with respect to the item “stroke recovery” is to be tested using the chi-square test (Mantel Haenzel corrected for gender and hemispheric location) by dichotomizing data into categories *improved* or *unchanged/deteriorated* with respect to change from baseline to follow-up, where improvement/clinically meaningful change is defined as any increase equivalent to 10 points of the total range of the scale. Un-ordered categorical data will be analyzed using the Mantel Haenzel chi-square approach. Analysis of covariance (ANCOVA) will be used to determine whether there are any differences between the control and intervention groups in post-intervention evaluation scores for continuous data, with baseline scores used as covariates in the analysis, and gender, hemispheric location and intervention as fixed factors. Qualitative data from the interviews and focus groups will be analyzed using content analysis as described by Malterud
[71]. Unsupervised algorithms will be used to analyze the plasma profiles in search for predictive biomarkers and biomarker patterns predictive of therapeutic success. For the primary and secondary analyses, missing data will be replaced using a conservative method, i.e. last observation carried forward (LOCF). All tests will be two-sided and with p<0.05 as a level of significance.

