### Current status

A total of 84 participants were randomised and have completed the intervention and the recruitment is expected to be completed by August 2013. The drop-out rate in the study has been 7%, including one participant allocated to T3 who suffered a new stroke, and another participant randomized to group T3, who deceased during the treatment period. Two of the drop-outs were randomized to group T3 and one was allocated to group T2. Recruitment proceeds and follow-up is on-going, trial results are expected in 2014.

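### The 80% power behind 41 per group does not reflect the rule that scores withdrawals as no change; with an equal 7% loss and 40 per arm it would be about 72–74% under the rates that reproduce 41

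*Protocol article*

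**What the plan says.** All references are to the protocol article.

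- **Sample size.** The calculation was made "with an alpha level of 5% and a power goal of 80" per cent. On the test it says "A Chi-square test was used for statistical calculations in Nquery 6.0". On the effect it says "An absolute difference between the two groups of 30% is defined to be a clinically meaningful difference", for the stroke recovery item of the SIS. The result is that "at least 41 patients would be required in each of the three groups for the results to satisfy the power criteria of 80" per cent, which is 3 × 41 = 123 in total. The proportions improving, any continuity correction and any drop-out allowance are not stated.
- **Study design (and Abstract).** "About 120 individuals will be consecutively and randomly allocated to one of three groups".
- **Statistical analysis.** The intention-to-treat set is all randomised patients with a baseline value of the primary outcome. "Those who withdraw will be assigned an outcome score identical to their baseline score i.e. no change". The stroke recovery item is dichotomised into improved versus unchanged or deteriorated, so a withdrawal is a non-improver who stays in the denominator. "All tests will be two-sided and with p<0.05 as a level of significance".
- **Current status.** "The drop-out rate in the study has been 7" per cent, with 84 randomised so far. The arm-level detail places most of the listed cases in T3 and one in T2.

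**The concern.** The sample size is derived for a 30-point difference, while the analysis rule pulls the proportion improving towards zero in any arm that loses patients. If the 30 points describe patients who are actually followed up, the difference that the test sees is smaller than the one used for planning, and 41 per group leaves no visible reserve for that. The planned total is also slightly below three times the stated minimum.

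The stake is interpretation. A null result would be read as coming from a trial with 80% power for a clinically meaningful difference, when the planned analysis might offer less.

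**Working it through.** **Inputs from the article:** two-sided 5%, power 80%, chi-square test, 30-point difference, 41 per group, about 120 in three groups, withdrawals scored as no change, interim drop-out 7%.

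**Assumptions:** equal allocation (40 per arm); the improvement rates p1 and p2; no continuity correction unless noted; the 30 points apply to completers; loss is equal across arms unless noted. The section also names LOCF for missing data. At the first post-intervention assessment both rules return the baseline value, so the choice does not matter there.

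**Step 1. Reproduce 41.** With p̄ = (p1 + p2)/2,

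n = [1.960·√(2p̄(1−p̄)) + 0.8416·√(p1(1−p1) + p2(1−p2))]² / (p2 − p1)²

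For 25% versus 55%: (1.3579 + 0.5551)² / 0.30² = 3.660 / 0.09 = 40.7, hence 41. The pair 45% versus 75% gives the same value by symmetry. For comparison, 20/50 gives 38.5, 30/60 gives 42.0 and 35/65 gives 42.4. With a continuity correction, 41 arises instead at 13/43 or 57/87.

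**Step 2. 41 versus 40 per arm, no loss.**

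Power = Φ{[(p2 − p1) − 1.960·√(2p̄(1−p̄)/n)] / √([p1(1−p1) + p2(1−p2)]/n)}

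At 25/55 or 45/75 this is 80.3% with n = 41 and 79.3% with n = 40. The difference is one percentage point.

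**Step 3. Apply the scoring rule.** If a fraction d of each arm withdraws and counts as not improved, both rates are multiplied by (1 − d). With d = 0.07, 25% and 55% become 23.25% and 51.15%, and the difference is 0.93 × 30 = 27.9 points. At n = 40:

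(0.279 − 1.960 × 0.10808) / 0.10348 = 0.649, and Φ(0.649) = 74.2%.

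Exact enumeration of the uncorrected test gives 74.6%.

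| Rates that give 41 | 40 per arm, no loss | 40 per arm, 3.6% loss | 40 per arm, 7% loss |
|---|---|---|---|
| 25/55, uncorrected | 79.3% | 76.8% | 74.2% |
| 45/75, uncorrected | 79.3% | 75.5% | 71.8% |
| 13/43, corrected | 79.6% | not computed | 74.6% |
| 57/87, corrected | 79.6% | not computed | 68.3% |

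The 3.6% column is 3/84, the smallest reading of the cases listed under Current status.

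**Step 4. Detectable difference.** At 40 per arm with an equal 7% scored as no change, 80% power needs a completer difference of 32.3 points at a 25% control rate and 32.9 points at 45%.

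**Step 5. Unequal loss.** At 25/55 and 40 per arm, assuming 84/3 = 28 per arm as denominator for the observed cases:

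- 7% lost in the active arm only: 67.9%.
- 2/28 lost in T3 and 1/28 in T2 (T2 versus T3): 79.6%.
- 2/28 lost in T3 and none in T1 (T1 versus T3): 84.3%.

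The last figure is above 80% only because control withdrawals are declared non-improvers, which widens the difference to 31.8 points. That is an effect of the imputation and adds no information.

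**The case against.** A reader might infer that the trial does not deliver 80% power, or that 41 contains no drop-out reserve. The article supports neither as a flat statement.

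- **An allowance may already be inside 41.** The rates are not given. A 20/50 scenario needs 38.5, and 38.5/0.95 = 40.5; a 15/45 scenario needs 36, and 36/0.88 = 40.9. Either rounds up to 41. At 40 per arm with an equal 7% loss these pairs give 76.9% and 80.6%. This is possible, but nothing in the Sample size section mentions an allowance.
- **The 30 points may already be the intention-to-treat difference.** Multiplying by 0.93 would then count withdrawals twice, and power would be 79.3% at 25/55. The section does not say which is meant, so this cannot be excluded; it is why the conclusion is conditional.
- **The 7% is an interim rate.** It was observed after the sample size was set, so it is no error in the original calculation. The listed cases (three to five, depending on reading) are 3.6% to 6.0% of 84 and do not clearly add up to 7%.
- **Equal loss is not the recorded pattern.** Most listed cases are in T3, and Step 5 shows that this raises nominal power. The point stands, although a gain of that kind is no reassurance.
- **123 is about 120.** This also stands: one patient per arm costs about one percentage point, so a claim of under-enrolment would not hold.

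Nor can one say that power is below 80% for every pair of rates. At 65/95, 40 per arm with a 7% loss still gives 82.9%.

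**Conclusion.** The point holds in conditional form. The 80% is stated without reference to the plan's own rule for withdrawals. If the 30 points describe completers and 7% withdraw equally from each arm, power at 40 per arm is about 74% (25/55) or 72% (45/75) for an uncorrected test, and about 75% (13/43) or 68% (57/87) for a corrected one. At 3.6% loss the uncorrected figures are about 77% and 75%. Almost all of the reduction comes from the scoring rule, not from 40 versus 41.

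The improvement rates, the form of the test, the meaning of the 30 points and the equality of loss are all assumptions. The size is therefore a range, and the article cannot settle whether actual power is above or below 80%. The matter deserves correction because the stated power will frame a null result and clarifying it is cheap.

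**What to change.** Revise the wording of the Sample size section; no extra patients are needed.

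1. Name the assumed control and treatment proportions, and say whether a continuity correction was used.
2. Say whether the 30 points refer to completers or to the intention-to-treat outcome with withdrawals scored as no change.
3. Use one total, 120 or 123, throughout.
4. Restate power under the withdrawal rule. If the rates were 25/55 or 45/75, uncorrected, and the 30 points refer to completers, suitable wording is: *with 40 per arm and an equal 7% of each arm scored as no change, power for a 30-point difference is about 72–74%; 80% power is reached for a difference of about 32–33 points.*

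The cost is a few sentences and a stated power that is less favourable than 80%. Design, enrolment and analysis stay as they are.
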